## 11. Trial Steering Committee

The terms of reference of the DFEND Trial Steering Committee are as follows:

1. To approve the final protocol for the DFEND trial. If changes are required to the final protocol, to agree these changes before they are put into effect.
2. To appoint an Independent Data Monitoring Committee if appropriate
3. To monitor and supervise the progress of the DFEND trial, paying particular attention to recruitment, adherence to the protocol and patient safety.
4. To review at regular intervals relevant information from other sources (e.g. other related trials) and to recommend appropriate action (such as changes to the protocol, additional patient information, and stopping the study).
5. To review reports of serious adverse events or unexpected adverse reactions during the course of the trial.
6. To endeavour to ensure that the trial is conducted at all times to the rigorous standards set out in the MRC Guidelines for Good Clinical Practice and in line with EU legislation for clinical trials involving medicinal products.
7. To inform the sponsor and funding body on the progress of the DFEND trial
8. To advise the Trial Management Group on publicity and the presentation of all aspects of the DFEND trial.

## 12. Data Monitoring Committee

The terms of reference the Data Monitoring Committee are as follows:

- Periodically review and evaluate the accumulated study data for participant safety, study conduct and progress.
- Make recommendations to the TSC concerning the continuation, modification, or termination of the trial, ensuring that ethical considerations are of prime importance.
- To consider any requests for release of interim data and to recommend to the TSC on the advisability of this.
- In the event of further funding being required, to provide the TSC and the funding body appropriate information and advice on the data gathered to date that will not jeopardise the integrity of the study.

### 13. Direct Access to Source Data and Documents

Source notes document each contact (personal, telephone or written) with participants, their carers, family or associated health care professionals (e.g. Trust staff, GPs). They include the case report forms used to record the baseline assessments and follow-up assessments as well as basic details, eligibility assessments and logs of capacity assessments, consent, blood taking and transport, randomisation documentation, adverse events, unblinding and data queries. They are specific to the trial and will not be confused with case notes. Each entry into the source notes will be traceable, signed and dated. However participation/adverse event data in the trial will be documented in the patient's case notes. For participants recruited from PIC sites study participation/adverse event data will be relayed to the GP/Clinical team in writing or by secure encrypted email correspondence.

The intervention assignment will be kept securely by those with access to it and separately from the source notes and the main trial database until the trial is closed and / or un-blinded.

All personal information collected on DFEND trial participants and on potential participants will be treated as confidential information and will be handled according to guidelines set out in this document, associated SOP, and in accordance with the terms of the Data Protection Act 1998. All electronic files containing personal information will be held only on password-protected computers. The computers themselves will be kept securely. All other trial information such as the TMF, source notes and data keys will also be stored in a lockable facility and only accessed by delegated DFEND trial staff.

Access to personal information that is neither coded nor anonymised will be restricted to the smallest number of DFEND trial staff that will allow the study to be conducted effectively (this is expected to include the researchers, Trial Manager, Data Manager and Principal Investigator but may include other trial staff as necessary). Access to encoded or anonymised data will be under the control of the Principal Investigator/Data Manager, and will include sharing data periodically with the funder as part of the funding agreement.

Trial Identification Numbers will be used in all correspondence; names will not be used in any data transmissions or correspondence except in those to the patient's carer or clinicians.

In accordance with ICH-Good Clinical Practice (GCP) guidelines, the DFEND investigators will permit trial-related monitoring and quality assurance audits providing direct access to source data documents. A programme of internal monitoring will also be conducted by the Data Manager / Trial Manager throughout the course of the trial. The monitoring and data management processes are described in more detail within the study-specific data management plan and monitoring plan respectively. These have been created in compliance with King's Health Partners Clinical Trial Office (KHP-CTO) SOPs.

The source notes will be retained until at least 15 years after the last publication is released for this trial. The source notes will be kept separate from general medical notes to reduce the likelihood of the notes being destroyed in error.

## 14. Ethics & Regulatory Approvals

The trial will be conducted in compliance with the principles of the Declaration of Helsinki (1996), the principles of ICH-GCP and in accordance with all applicable regulatory requirements including but not limited to the Research Governance Framework and the Medicines for Human Use (Clinical Trial) Regulations 2004, as amended in 2006 and any subsequent amendments.

This protocol and related documents will be submitted for review to the Research Ethics Committee (REC), and to the Medicines and Healthcare products Regulatory Agency (MHRA) for Clinical Trial Authorisation.

The Chief Investigator will submit a final report at conclusion of the trial to the KHP-CTO (on behalf of the Sponsor), the REC and the MHRA within the defined timelines.

## 15. Quality Assurance

Monitoring of this trial will be to ensure compliance with Good Clinical Practice and scientific integrity will be managed and oversight retained, by the KHP-CTO Quality Team.

## 16. Data Handling

The Chief Investigator will act as custodian for the trial data. The following guidelines will be strictly adhered to:

- Patient data will be anonymised
- All anonymised data will be stored on a password protected computer.
- All trial data will be stored in line with the Medicines for Human Use (Clinical Trials) Amended Regulations 2006 and the Data Protection Act and archived in line with the Medicines for Human Use (Clinical Trials) Amended Regulations 2006 as defined in the Kings Health Partners Clinical Trials Office Archiving SOP.

The primary objective of good data handling and record keeping is to ensure that data collected on participants in the trial are accurate and complete and unbiased with respect to the trial intervention allocation.

Source data will be entered directly on to paper source data workbooks and then transferred to an electronic CRF via a customised Macro database created and maintained by the KCTU. The data entry screens will resemble the paper source document forms as closely as possible to minimise transcription error. All research staff will be advised to take care to ensure a thorough audit trail is maintained throughout the trial.

All participant data will be assigned a five digit patient identification number (PIN). The PIN will have no relation to the participants name or date of birth or any other patient identifier and will

be used on all study questionnaires and blood samples - no patient identifiable details will be recorded on the samples therefore the data gathered would not be identifiable to a third party and only the research team would be able to identify this data.

All study booklets will be stored in temperature managed, fireproof filing cabinets in access-controlled offices.

Access to the EDC (MACRO) database will be restricted to study researchers. Each researcher will have a personal username and password that only they know, thereby limiting unauthorised access to the electronic data, this will also allow for a detailed audit trail to be maintained within Macro.

## 17. Data Management

A data management plan will be written to detail central monitoring and data-integrity checking processes. All computers that will be used will have installed anti-virus software and staff will be informed of the importance of data protection and safe handling of data. There will be a manual and training slides provided to each end user to accompany the MACRO software to ensure each user is appropriately trained. The Macro development team will also be contactable if there are any issues with the database throughout the trial which will allow for proper database maintenance to occur.

As previously mentioned, all trial data will be collected on paper CRF and then transferred on to an electronic database. This will allow for a double-check of the data for good practice.

#### Flow Diagram of Data Handling Process:

[figure not shown]

## 18. Publication Policy

No report, either verbal or written, will be made without the prior approval of the Trial Steering Committee.

The trial team comprising all investigators, the trial manager, the trial statistician and members of the trial management group will be listed on all papers resulting from the main Statistical Analysis Strategy agreed by the TSC. Those contributing to the writing of papers arising from the Statistical Analysis Strategy will be included as co-authors on the relevant papers.

Independent members, other members and observers of the Trial Steering Group and the Data Monitoring and Ethics Committee (if appointed), will be acknowledged on all primary papers.

Research findings will be disseminated via peer-reviewed journals, conferences, internal reports and user group meetings. When the project is complete we will be able to provide all participants with a general summary of our research through a project newsletter. Our research study will also be described on the Institute of Psychiatry, Psychology and Neuroscience (IoPPN) general website ([www.kcl.ac.uk](http://www.kcl.ac.uk)), under the Department of Psychosis Studies.

## 19. Insurance / Indemnity

Arrangements for negligent harm and for compensation are covered by insurance and indemnity policies held by King's College London and the SLAM NHS Foundation Trust.

## 20. Financial Aspects

Funding to conduct the trial is provided by the Stanley Medical Research Institute (non-commercial).

### **Purpose and Scope of Statistical Analysis Strategy**

This document details the presentation and analysis strategy for the primary papers reporting results from the DFEND trial. It is intended that the results reported in these papers will follow the strategy set out herein; subsequent papers of a more exploratory nature will not be bound by this strategy but will be expected to follow the broad principles laid down for the principal paper(s). These principles are not intended to curtail exploratory analysis or to prohibit sensible statistical and reporting practices, but they are intended to establish the strategy that will be followed as closely as possible, when analysing and reporting the trial. Reference was made to the trial protocol (V9.2 01.10.2018), ICH [1] guidelines on Statistical Principles (E9) and CONSORT [2] guidelines.

This document contains up to date statistical analysis plans (with version numbers and dates).

- A) Quantitative Analysis Plan
- B) Schedule of Assessments and Measures

## **1. *Description of the trial***

### **1.1 Principal research objectives to be addressed**

We hypothesise that optimal vitamin D status could be neuroprotective in those with first episode psychosis (FEP).

#### Primary objectives

- To determine whether the addition of 120,000 IU monthly of vitamin D (cholecalciferol) supplement to standard treatments is more efficacious than placebo in improving outcomes (Positive and Negative Syndrome Scale (PANSS) total score) at 6-months post randomisation follow up in those with First Episode Psychosis.

#### Secondary objectives

To examine the following broader range of clinically-relevant outcomes:

- PANSS total score at 3 months
- PANSS subscores at 3 and 6 months:
  - Positive Scale
  - Negative Scale
  - General Psychopathology Scale
- Global Assessment of Function (GAF) at 6 months
- Calgary Depression Scale (CDS) at 6 months
- Cardiovascular risk markers at 6 months:
  - Waist circumference (cm)
  - BMI (kg/m^2)
  - HbA1c (mmol/mol)
  - Total Cholesterol (mmol/L)
  - CRP (mg/L)
- 25-hydroxyvitamin D (25OHD) Concentrations at 6 months

We will examine these outcomes in (a) all participants and (b) in a subgroup of patients with suboptimal vitamin D concentrations at baseline (except for 25OHD blood concentration levels).

### **1.2 Trial design including blinding**

We propose a randomised, double-blind, placebo-controlled, parallel-group trial of Vitamin D supplementation compared to placebo in people presenting with their first episode of psychosis. Study participants will be on active study treatment for a maximum of 6 months.

The trial will be double blind. Active and placebo oral medication will be produced and packaged identically. Clinicians and research workers completing baseline, clinic attendance assessments and all follow-ups will be blind to group allocation, as will patients and pharmacists. This design will ensure that the study has a high level of both treatment integrity

## DFEND

(delivery of the treatment as intended) and treatment differentiation (treatment conditions differed from one another in the intended manner). The trial has two groups:

- Group A: 50% of participants will be randomised to Active Treatment with Cholecalciferol (vitamin D3), 120,000 IU per month (equivalent to 4,000 IU per day), given orally as Vigantol® oil by Merck Sereno GmbH, Germany (cholecalciferol dispersed in triglyceride oil as vehicle; 8 ml bottles, containing 20,000 IU cholecalciferol per 1ml drop, and administered as 6mL given in a graduated oral syringe by a fully trained member of the research team).
- Group B: For the 50% receiving placebo, we will use identical bottles containing an organoleptically matched triglyceride oil (Miglyol® 812 oil). Administration of the placebo will be identical to the active treatment.

Figure 1. Trial design flow diagram

[figure not shown]

### 1.3 Method of allocation of groups

An online randomisation service will be provided by the King's Clinical Trials Unit. Randomisation will take place after collection of baseline measures. The unit of randomisation will be the individual participant. Randomisation will be at a 1:1 ratio and the method of randomisation will be stratified randomisation with randomly varying block sizes of 2-4 where the stratification factor is ethnicity (with 2 levels: White, Other).

We chose to balance treatment arms by ethnicity as this is thought to predict outcomes. There are no known predictors of PANSS in our target population. However, blood vitamin D concentration varies by ethnicity; and we hypothesize that blood vitamin D concentration mediates any effect of vitamin supplement. Thus, ethnicity was chosen as a randomisation stratifier.

### 1.4 Duration of the treatment period

Participants will receive a monthly dose of either Vigantol Oil 120,000 IU per month (equivalent to 4,000 IU per day) or placebo.

The end of the trial will be defined as the last patient's post 6-month visit telephone call. Each participant will remain on the trial until they have each completed the post 6-month visit telephone call. The study will run from December 2015 until December 2019 to ensure that each participant has 6 months of exposure to either the active or placebo treatment.

### 1.5 Frequency and duration of follow-up

Primary and secondary measures will be taken at baseline (pre-randomisation), and 6 months post-randomisation, there will be an additional PANSS measure at 3 months post-randomisation. Safety outcomes will be additionally collected at 3 months post-randomisation.

### 1.6 Visit windows

For the follow-up assessment at 6 months a visit window of -4/+6 weeks will be set to ensure follow-up data is collected. For routine safety blood visits, a -2 week window will be adhered to, but an upper time frame will not be specified for collecting the safety bloods as these must be performed.

### 1.7 Data collection

#### Eligibility screening

The study population will be patients in their first episode of psychosis (FEP) defined as first presentation to services within the last three years.

#### Inclusion Criteria

All patients within psychosis services, including Early Intervention Services (EIS) and First Episode Psychosis (FEP) inpatient units who meet the following criteria will be invited to participate in the study:

1. Aged between 18-65 years old including women of child-bearing age
2. Having a diagnosis of functional psychosis FEP defined according to ICD-10 criteria for psychosis (codes F20-29 and F30-33).
3. Willing to agree to refrain from taking multivitamin or non-study vitamin D supplements that exceed 400IU/day throughout the study

## DFEND

4. Willing to give a blood vitamin D sample at baseline
5. Patients who are able and have given written informed consent.

### Exclusion Criteria

1. Known intolerance of Vitamin D2 or D3 or known allergy to any of the trial medications
2. Those who are currently taking vitamin D supplements at a dose exceeding 400IU/day
3. Those who have taken cardiac glycosides, calcium channel blockers or oral, intramuscular or intravenous corticosteroids, bendroflumethiazide, isoniazid and rifampicin in the past one month
4. Known active tuberculosis, sarcoidosis, hypo or hyperparathyroidism, past or present nephrolithiasis (renal stones), suspected or diagnosed hepatic or renal dysfunction, any malignancy other than non-melanoma skin cancer not in remission for  $\geq 3$  years, calcium disorders
5. Baseline corrected serum calcium  $> 2.6$  mmol/L
6. Patients with known history of hypercalcaemia
7. Pregnant or breast-feeding women and women planning a pregnancy
8. Patients lacking the capacity to provide written informed consent
9. Those who do not have sufficient English to complete the core assessments with the available assistance

### Measures

A detailed description of data collected will be given in the Schedule of Assessments and Measures (section B of this document). What follows is a brief overview to aid understanding of the analysis plan.

### Baseline

- Eligibility and consent
- Socio-demographics
- Duration of untreated psychosis
- Current medication
- Vitamin supplementation
- Anthropometrics
- Blood sampling full blood count
- Urine pregnancy test
- Smoking history
- Sun exposure measure
- IPAQ
- Fitzpatrick Skin Type Questionnaire
- Vitamin D food questionnaire
- Blood sampling for calcium levels

### Primary outcome measures at baseline, 3 months and 6 months post randomisation

- PANSS Total Score

### Secondary outcome measures at baseline, 3 months and 6 months post randomisation

- PANSS Positive scale sub-score
- PANSS Negative scale sub-score

## DFEND

- PANSS General Psychopathology sub-score

### Secondary outcome measures at baseline and 6 months post randomisation

- GAF score
- CDS score
- Waist circumference (cm)
- BMI (kg/m^2)
- HbA1c (mmol/mol)
- Total Cholesterol (mmol/L)
- CRP (mg/L)
- Blood sampling vitamin D concentrations

### Mediators of treatment

Vitamin D concentrations may be a mediator of treatment effect on PANSS. If Vitamin D supplementation increases blood concentrations, we could demonstrate that any change in PANSS is due to changes in blood concentrations.

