#### Could low vitamin D impair recovery from first episode psychosis?

Previously, we proposed that first generation dark-skinned migrants exposed to both “social defeat” and hypovitaminosis D may be less able to buffer stress-related adverse brain outcomes (McGrath, 2010). In light of the neuroprotective properties of vitamin D (especially those related to dopaminergic pathways), and in light of the recent findings that vitamin D supplementation can slow the progression of dopamine-related neurodegenerative disorders like PD, we believe that there is now a strong case to examine whether vitamin D supplementation can optimize outcomes in first episode psychosis (FEP) (McGrath, 2010).

A recently published systematic review (based on seven studies) has confirmed that those with psychosis are significantly more likely to have low concentrations of vitamin D (BelvederiMurri et al., 2013). Crews et al., 2013 recently examined vitamin D status in a sample of 69 patients with FEP and 69 controls matched on age, sex and ethnicity. FEP patients had nearly a three-fold increased risk of vitamin D deficiency (OR= 2.99, 95% CI=1.33-6.74). In the FEP group, over a third (36.2%) had frank vitamin D deficiency (less than 25 nmol/L) while an additional 25% of FEP were classified as having vitamin D insufficiency (between 25 and 50 nmol/L). As pilot data for this application, we undertook a preliminary analysis of data currently being collected for the IMPACT study ([www.kcl.ac.uk/iop/depts/ps/research/clinicaltrials/IMPACT.aspx](http://www.kcl.ac.uk/iop/depts/ps/research/clinicaltrials/IMPACT.aspx)). Low vitamin D at baseline predicted poorer function ( $r=.327$ ,  $p=0.045$ ) and higher Calgary depression scores ( $r=.404$ ,  $p=0.012$ ) at 12 months. A significant relationship between baseline Vitamin D and 12 months PANSS did not persist once adjusted for age, sex, ethnicity and season of sampling, but mean vitamin D between baseline and 3 months tended towards an association with PANSS

total ( $r = -.356$ ,  $p = 0.063$ ) and negative ( $r = -.342$ ,  $p = 0.059$ ) scores at 12 months, and had a significant relationship with 12 month Depression ( $r = -.369$ ;  $p = 0.038$ ) and GAF ( $r = .491$ ,  $p = 0.002$ ).

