## 7.2 Laboratory Tests

All blood samples will be obtained by a trained phlebotomist.

Blood will be taken for 25OHD concentration at baseline and 6 months but this assay will not be performed until the trial is complete. This is to ensure that researchers and clinicians are blind to baseline vitamin D status and that the patients will be offered standard clinical treatment. Additionally there is clinical equipoise regarding vitamin D supplementation in this group (i.e. the uncertainty of the intervention's efficacy versus the potential that leaving participant's vitamin D deficient will cause harm). This strategy has been employed successfully by one of the investigators ([name]) elsewhere (Gaughran et al., 2007). At the end of the study, once all data is analysed we will inform the participant's respective clinical team and/or GP of their vitamin D levels at last testing, noting that it may be some time after that test. Appropriate recommendations for post-study vitamin supplementation will be made by patient's GP or clinical team. Once the study is complete, serum samples will be shipped to the funder (Stanley Medical Research Institute) as part of the funding agreement, in an anonymous format. The Biomedical Research Centre (BRC) will store this sample until it is ready to be shipped to America. Clinical markers for cardiometabolic and general health will be tested from the same bleed (and shared with the clinical team with the patient's permission), and samples stored to later test for immune/inflammatory markers. Safety tests include calcium and if indicated parathyroid hormone test.

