### Power calculation

Based on recently collected PANSS Total score in FEP patients collected as part of the Physical Health and Substance Use Measures in first episode Psychosis (PUMP) study (n = 190), the mean (and standard deviation) score was 58.1 (15.0) units. Based on the number of new cases presenting to FEP services and based on the annual counts of FEP patients recruited into similar studies, we predict that we will recruit 120 patients per year (i.e. 240 over two years).

The primary intention to treat (ITT) analyses will compare two equally sized treatment arms, treatment or placebo on the PANSS scale at 6 months post-randomisation. For the power analyses, we modelled two plausible scenarios. For the primary outcome (six-month follow-up), we assumed a 20% attrition proportion. After 20% attrition the sample size is 192, 96 in each trial arm).

Based on alpha = 0.05 and power = 80%, samples between 200 and 180 participants will be able to confidently detect mean PANSS total score group differences of between 6 and 6.3 units. This equates to a standardised effect of size of approximately 0.4 to 0.42. Considering

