### 1.9 Brief description of proposed analyses

Analyses will be carried out by the trial statistician. The trial statistician will remain blind until all analyses are completed. The analysis of the secondary outcome of blood sampling vitamin D concentrations at 6 months will be carried out after all other analyses are completed as there is a high expectation that mean concentration will be higher in the intervention group.

The primary analyses of efficacy will be based on the intention-to-treat sample, utilising all available follow-up data from all randomised participants. The significance level will be 5% (2-sided) for all specified main and secondary analyses with estimates and confidence intervals presented for all effects.

All descriptive analyses, recruitment rate, consent rate, loss to follow-up, departures from randomised treatment and the prevalence of serious adverse events will be reported post-randomisation and summarised by treatment arm over the course of the study. All causes of withdrawal from randomised treatment will be reported.

The main objective of the statistical analyses is to assess the effect of vitamin D supplementation on the primary outcome PANSS total Score at the 6-month follow-up time point. To this end linear mixed modelling (LMM) will be employed.

Treatment effects on secondary outcomes will be using generalized linear models allowing for non-normal data where necessary. Treatment arm, baseline measurement of the outcome and randomization stratifier (ethnicity) will be included as covariates.

Average treatment effects (ATE) with the FEP population will be estimated at 3 and 6 months for the primary outcome and at 6 months for all secondary. We will also estimate subpopulation (baseline vitamin D insufficient and sufficient) specific treatment effects for the primary outcome and all secondary outcomes, except for 25OHD blood concentration levels, by use of an interaction of baseline vitamin D insufficiency status with treatment group in the statistical models.

We expect there to be some missing data in the post-treatment outcomes variables. The LMM analyses are based on maximum likelihood and will provide valid inferences under a missing at random (MAR) missingness mechanism. We will explore predictors of missingness, if deemed suitable for adjustment we will include these as explanatory

DFEND

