### **Mechanism of action**

The study is based on the theoretical model that vitamin D supplementation might improve psychotic symptoms (PANSS) by increasing blood vitamin D levels to sufficient levels. We wish to investigate this empirically by partitioning any detected vitamin D supplement effect on PANSS into two components: (a) A part that is mediated via changing blood concentration levels (indirect effect) and (b) a non-mediated part (direct effect). To this end we will employ appropriate mediation methods such as the product of coefficients method or linear structural equation models. These methods rely on the assumption that all confounders of the blood level – PANSS path have been measured and included in the models [6].

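### 25OHD after randomisation is measured only at the visit that yields the primary PANSS, so the mechanism analysis can show results consistent with mediation but cannot demonstrate that PANSS change is due to blood levels

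*Combined protocol and SAP*

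**What the plan says.** SAP section 1.7, under Mediators of treatment, calls vitamin D concentration a possible mediator and adds: "If Vitamin D supplementation increases blood concentrations, we could demonstrate that any change in PANSS is due to changes in blood concentrations".

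SAP section 3.1.2, under Mechanism of action, would split any detected effect on PANSS into a part passing through blood level and a remainder, by product of coefficients or linear structural equations. It gives one condition: "These methods rely on the assumption that all confounders of the blood level" to PANSS path are measured and entered in the models. It does not list those confounders or mention time order.

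On timing, Protocol section 7.2 says: "Blood will be taken for 25OHD concentration at baseline and 6 months". Protocol Table 1 and the SAP schedule (part B) agree. PANSS is rated at baseline, 3 and 6 months. The routine 3-month blood sample is for calcium, and Protocol section 10.2 says the 12-month data from early participants will not be analysed.

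The sensitivity analyses in SAP sections 1.9, 3.1 and 3.1.4 cover missing outcomes, departures from randomised treatment and changes in eligibility. None concerns mediation.

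**The concern.** Randomisation identifies the effect of arm on 25OHD and the effect of arm on PANSS. It does not identify the path from 25OHD to PANSS, which rests on the association within arms. With both measured at one visit, that association can run either way. Someone more unwell by month 6 may go outdoors less, eat less well, be less active or miss doses, and so have lower 25OHD. The documents leave room for this: Protocol section 7.1 collects sun exposure, activity and diet as influences on vitamin D, and section 5.6 lets participants continue after a missed dose.

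Product of coefficients multiplies the within-arm slope by the arm difference in 25OHD. SAP section 1.9 expects a higher mean in the intervention group. The larger that difference, the more a small non-causal slope is magnified. The risk is a published mechanism claim with the wrong causal direction, on what the SAP calls the trial's theoretical model.

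**Working it through.** **Inputs from the documents.** PANSS: "the mean (and standard deviation) score was 58.1 (15.0) units". Analysed sample after 20% attrition: 192, or 96 per arm. Test level: "The significance level will be 5% (2-sided) for all specified main and secondary analyses".

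**Reproducing the plan's figure.** The power section says "samples between 200 and 180 participants will be able to confidently detect mean PANSS total score group differences of between 6 and 6.3 units" and "This equates to a standardised effect of size of approximately 0.4 to 0.42". The normal approximation gives (1.960 + 0.842) x 15 x sqrt(2/100) = 5.94 for N = 200 and (1.960 + 0.842) x 15 x sqrt(2/90) = 6.26 for N = 180. The t version gives 5.97 and 6.30. The figures reproduce, and 6 points (d = 0.40) serves as the total effect below. The plan gives no figure for the mediation analysis.

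**Assumed input.** D is the arm difference in 6-month 25OHD in within-arm SDs. The documents do not state it, so I use 1 to 2. The only guide to the spread is the case-control study in Protocol section 3: 36.2% of patients below 25 nmol/L and a further 25% below 50. Under normality the SD is 25 / (0.285 + 0.353) = 39 nmol/L, so D = 1 means about 39 nmol/L and D = 2 about 78. This is rough: the implied mean is also about 39, which would put some 16% of values below zero. Adjusting for baseline 25OHD would reduce the residual SD and raise D.

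**No true mediation, two versions.** The whole 6-point effect is direct.

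1. Residual correlation r between 25OHD and PANSS, direction unspecified: false indirect effect = r x 15 x D.
2. PANSS lowers 25OHD explicitly, with correlation size |r|: false indirect effect = -|r| x (D + 0.4|r|) x 15, and apparent share mediated = |r| x (D + 0.4|r|) / 0.4.

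With r = -0.20:

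| D | Version 1 (points) | Version 2 (points) | Share (version 2) | Indirect significant (version 2) | Indirect significant, direct not (version 2) |
|---|---|---|---|---|---|
| 1 | -3.0 | -3.2 | 54% | 77% | 66% |
| 1.5 | -4.5 | -4.7 | 79% | 79% | 76% |
| 2 | -6.0 | -6.2 | 104% | 80% | 77% |

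The last two columns come from 3,000 simulated trials per row with a Sobel test. Version 1, simulated in the same way, gave about 78% significant, and 63%, 75% and 75% for the last column.

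**Hand check of the significance rate.** The t value for the 25OHD slope is 0.20 x sqrt(189) / sqrt(0.96) = 2.81. The t value for the arm difference is D / sqrt(2/96), or 6.93 at D = 1 and 13.86 at D = 2. The Sobel z is 1 / sqrt(1/2.81² + 1/6.93²) = 2.60 and, at D = 2, 2.75. These give approximate rejection rates of 74% and 79%, in line with the simulations.

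**Other correlations.** At r = -0.10 (version 1), the false effect is -1.5 points (D = 1) to -3.0 points (D = 2), significant in about 26 to 27% of trials. The |r| at which zero mediation looks like exactly 100% (version 2) is 0.35 at D = 1, 0.25 at D = 1.5 and 0.19 at D = 2.

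**What adjustment can do.** Assume PANSS scores correlate 0.6 between every pair of visits. Baseline and 3-month PANSS then explain 2 x 0.36 / (1 + 0.6) = 45% of the within-arm variance at 6 months. In simulation, adjusting for both cut the false effect by about 45%. That helps, but the direction remains unresolved.

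**The case against.** Mediation is not a listed objective or endpoint in Protocol sections 4.1 and 4.2 or SAP section 1.1. It is run only on an effect already detected, and no treatment comparison depends on it. The section 1.7 sentence sits in an overview and follows a cautious statement that concentration may be a mediator. Section 3.1.2 already requires the confounders to be measured and included, and many are collected. All this stands and limits the importance of the point. It does not supply time order, and the sentence still promises a demonstration.

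A reader might infer four stronger things that the documents do not support.

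- That a modest reverse link would always look like full mediation. At a correlation of -0.20 that needs a shift of about 2 SD. At 1 SD the point estimate shows about half.
- That the pilot proves the path is confounded or reversed. The baseline vitamin D association with 12-month PANSS "did not persist once adjusted for age, sex, ethnicity and season of sampling", which is compatible with confounding but does not establish it. The other pilot correlation (-0.356, p = 0.063) relates mean vitamin D over baseline to 3 months to PANSS at 12 months. Vitamin D comes first there, so it is no evidence of PANSS acting on 25OHD.
- That the mediation model adjusts only for the baseline outcome and ethnicity. Those are the treatment-effect models in SAP sections 1.9 and 3.1.1; the mediation model is described separately, without a covariate list.
- That mediation should be claimed only if it survives a correlation of -0.36. The pilot value alone removes 0.356 x 15 = 5.3 points at 1 SD and 10.7 at 2 SD, so a genuine, fully mediated 6-point effect would nearly vanish or reverse.

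**Conclusion.** The point holds in a limited form. The only post-randomisation 25OHD value to be analysed is contemporaneous with the primary PANSS, so the planned analysis cannot establish direction, and the statement in SAP section 1.7 is too strong. A non-causal within-arm correlation of -0.20 could produce a false indirect effect of about -3 to -6 points, significant in about 77 to 80% of trials. That rests on 96 per arm, SD 15, a wholly direct 6-point effect, no covariate adjustment and an assumed arm shift of 1 to 2 SD. Neither the shift nor the size of any reverse link is given in the documents, so this shows vulnerability and does not predict what the trial will find. A reader might infer that the efficacy result is in doubt. It is not: the arm comparison on PANSS does not use 6-month 25OHD.

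**What to change.** 1. In SAP section 1.7, replace the sentence on demonstrating cause. Say that the analysis is exploratory, can show only that results are consistent with mediation, and cannot establish direction because 25OHD and PANSS are measured at the same visit.
2. In SAP section 3.1.2, state the time-order assumption (no effect of PANSS on 25OHD) beside the confounding assumption. List the adjustment variables for the 25OHD-PANSS path: baseline 25OHD, baseline and 3-month PANSS, age, sex, ethnicity, season of sampling, and baseline sun exposure, activity, diet, BMI and smoking. Do not adjust for 6-month BMI, which is a post-treatment endpoint.
3. Add a descriptive table of the indirect effect over a stated range of residual 25OHD-PANSS correlation, marking the value at which it reaches zero. Set no pass/fail threshold.

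The cost is SAP wording, one extra table and a weaker mechanism claim. Adjusting for 3-month PANSS may remove part of a true effect already present by month 3, so report results with and without it. Because the 25OHD assay waits until the trial is complete (Protocol section 7.2), these changes can still be made before any 25OHD data exist. Adding 25OHD at month 3 is not proposed: with the SAP dated April 2019 and the study ending in December 2019, few participants could still contribute.
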